### 3.7. Data Collection

Data will be collected primarily through a face-to-face interview with an open-ended structured questionnaire. The interview team will comprise graduates in social science, public health, demography, and statistics with extensive experience in survey techniques, along with two experienced supervisors who will oversee the survey. They will all undergo four days of mandatory training and two days of practical sessions focused on the questionnaire content, techniques to obtain more information from study subjects, and strategies for acquiring complete and valid data. An operational manual will be provided to both interviewers and supervisors to ensure clarity on the research purpose. The supervisor will be responsible for regularly monitoring the intervention process. The details about the data collection time point are mentioned in Table 2.

At baseline, after obtaining informed consent by the interviewer, data will be collected on the self-reported basic socioeconomic and demographic characteristics of the patients, such as age at the completion of the questionnaire, gender, highest level of education completed, occupation, religion, and marital status. Also, the basic characteristics of the CP (age, gender, and working experience in the community pharmacy in years) will be collected. Information on disease profiles will be obtained by face-to-face direct interview and used to inform the consultation at each stage. The following data will be requested from patients and CP at baseline and 12 months via questionnaire or pre-defined data collection form (as appropriate):Clinical factors of the patients [time since diagnosis of hypertension in years; types of concomitant antihypertensive medications; development of any hypertension-related complications such as coronary heart disease (CHD), and heart failure and stroke; in the previous six months: (i) occurrence of any adverse health condition related to hypertension requiring hospitalization; (ii) total number of days in hospital following admission; and (iii) total number of visits to doctors for hypertension and its related complication management;Organizational information of the community pharmacies (number of visits from hypertensive patients per month in last six months, number of hypertensive cases referred to hospital due to complications in last six months);Quality of life measure (EuroQol EQ-5D-5L) [28].

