### 3.9. Cost-Effectiveness Analysis

The intervention cost will be calculated by considering average times (including both patient contact and non-contact) for the pharmacist at each consultation (baseline, at 6 months, at 12 months, and any additional consultations). Participant attendance rates, recorded by the pharmacist delivering the intervention, will be combined with the estimated cost per consultation, allowing for the total cost of all consultations to be calculated for each participant. Pharmacists will receive proper training to convey the intervention using a tablet and other equipment (e.g., booklet, BP record book) from each participating pharmacy. All of these items will be documented along with their associated costs, including pharmacist time (cost calculated as above), equipment costs, and consumables for blood pressure measurement. Pharmacist training costs will also be measured. To calculate the per-patient total intervention costs, all of the above-mentioned costs will be equally divided among all intervention group participants and then added to the aforementioned per-patient total consultation cost. The cost of each activity will be valued using standard rates. Finally, the cost per unit (mmHg) of blood pressure reduction and/or cost per HRQoL gain will also be measured.

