### 3.13. Statistical Analysis

All outcomes will be analyzed using the intention-to-treat principle. Descriptive statistics will be used to present baseline characteristics and outcome variables. Percentages and frequencies will be used for categorical variables, and means and standard deviations will be used for continuous variables. Baseline characteristics between the two arms will be compared with chi-square or Fisher’s exact test, as appropriate. A multilevel mixed model will be used to compare the differential changes in each outcome across the time points (T1, T3, and T5) to measure the primary and secondary outcomes. We will analyze group changes (with individual pharmacies treated as a random effect) using multivariable mixed linear and non-linear regression for normally and non-normally distributed data to account for the cluster randomization effects. Point estimates from cluster-adjusted models will be reported with 95% confidence intervals. Additionally, subgroup analysis will stratify data based on hypertension-related complications and the number of associated medications to estimate the effect of the interventions. For all two-tailed statistical tests, *p*-value < 0.05 will be considered statistically significant. We will perform all statistical analyses using R (version 4.1) and Stata software (version 17.0).

A cost-effectiveness analysis will be performed on the average total cost incurred in both arms, and incremental cost-effectiveness ratios expressed as incremental cost per (1) 1, 5, or 10 unit (mmHg) decrease in blood pressure; (2) one hospital admission reduced; (3) 1 day of hospital stay reduced over the previous 6 months among the survivors; and (4) HRQoL using data from EQ-5D-5L and mortality. We will calculate all cost data in US dollars, using the non-subsidized cost as of the study’s commencement.

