** *Baseline characteristics (Control and intervention group)* **												
Sociodemographic profile						x			x			x
Dietary habits						x			x			x
Physical exercise habits						x			x			x
Knowledge of hypertension						x			x			x
Direct treatment cost information						x			x			x
Indirect treatment cost information						x			x			x
HRQoL (EuroQoL-5D)						x			x			x

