** *Outcome measurements (Control and intervention group)* **												
*Primary outcome*												
Change in SBP and DBP									x			x
*Secondary outcome*												
BP controlled to target									x			x
Composite outcome of death or hospital admission									x			x
Improvement in knowledge									x			x
Changes in lifestyle									x			x
Changes in drug adherence									x			x
HRQoL gained									x			x
Cost per unit of BP reduction									x			x
Cost per HRQoL gained									x			x

HRQoL, health-related quality of life; SBP, systolic blood pressure; DBP, diastolic blood pressure; BP, blood pressure.

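### Section 3.7 collects hospital-use data at baseline and 12 months while Table 2 implies months 6 and 12, and one cost ratio may set a 12-month cost against six months of hospital days

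*Protocol article*

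**What the plan says.** Section 3.7 introduces its list of items with "The following data will be requested from patients and CP at baseline and 12 months". The list includes "in the previous six months: (i) occurrence of any adverse health condition related to hypertension requiring hospitalization", then days in hospital and number of doctor visits under the same six-month clause, and finally the EQ-5D-5L. The same section also says "The details about the data collection time point are mentioned in Table 2".

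Table 2 marks "Composite outcome of death or hospital admission" at months 6 and 12 in both arms, and "HRQoL (EuroQoL-5D)" at months 0, 6 and 12. It has no row named for hospital days or doctor visits. It does have rows for direct and indirect treatment cost at months 0, 6 and 12.

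Section 3.8 defines the composite as death from any cause, or admission for coronary disease, heart failure or stroke, with no six-month limit. It lists physician visits and hospital admissions as utilisation measures.

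Section 3.13 models "differential changes in each outcome across the time points (T1, T3, and T5)", which are months 0, 6 and 12. Its cost-effectiveness paragraph takes the mean total cost in each arm, states no window for it, and gives as ratio (3) the cost per "1 day of hospital stay reduced over the previous 6 months among the survivors". Section 3.9 builds the intervention cost from consultations at "baseline, at 6 months, at 12 months, and any additional consultations".

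**The concern.** There are two separate problems.

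The first is timing. A six-month look-back at 12 months reaches back only to month 6. If the questions are asked at baseline and 12 months only, non-fatal admissions, hospital days and doctor visits in the first half of follow-up fall between the two interviews. The composite is meant to cover the whole follow-up, and the planned model expects a month-6 value for each outcome. The Introduction presents the effect on admissions and the cost-effectiveness as what is new in this trial, so these are not incidental items.

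The second is ratio (3). Its effect is limited to six months and its cost is not. If the cost is the 12-month total, the result is not the cost per hospital day avoided over the trial, and a reader comparing it with the other ratios would not see the difference.

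**Working it through.** The plan states no figure on this point, so the check compares schedules and windows.

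**Step 1: the schedules side by side**

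| Item | Section 3.7 | Table 2 |
|---|---|---|
| Hospitalised adverse conditions | months 0 and 12, six-month look-back | composite at months 6 and 12 |
| Hospital days | months 0 and 12, six-month look-back | no named row; treatment-cost rows at months 0, 6 and 12 |
| Doctor visits | months 0 and 12, six-month look-back | no named row; treatment-cost rows at months 0, 6 and 12 |
| EQ-5D | months 0 and 12 | months 0, 6 and 12 |

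**Step 2: follow-up months covered by the look-back**

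- Section 3.7 taken literally: the windows are months -6 to 0 and months 6 to 12. Within follow-up (months 0 to 12) they cover 6 months, so 12 - 6 = 6 months are not asked about, and 6/12 = 50%.
- Table 2 with the six-month look-back at each follow-up survey: the windows are months 0 to 6 and months 6 to 12. They cover 6 + 6 = 12 months, so none is missed.
- Deaths do not depend on the look-back under either schedule.

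**Step 3: ratio (3)**

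Section 3.13 gives no cost window. Twelve months is inferred from Section 3.9 (consultations at baseline, 6 and 12 months) and Section 3.8 (a 12-month horizon for the blood-pressure and quality-of-life ratios).

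Let C be the incremental cost over 12 months, and D1 and D2 the hospital days saved in months 0-6 and 6-12.

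- Ratio as stated, at the 12-month analysis: C / D2.
- Ratio with matched windows: C / (D1 + D2).
- Stated divided by matched: (D1 + D2) / D2 = 1 + D1/D2.

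The documents give neither D1 nor D2. The following are assumed cases, shown only for the range:

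| Assumption | 1 + D1/D2 |
|---|---|
| D1 = -0.5 × D2 (extra days early, savings late) | 0.5 |
| D1 = 0 (no early savings) | 1.0 |
| D1 = D2/3 (three quarters of savings in months 6-12) | 1.33 |
| D1 = D2 (even over the year) | 2.0 |
| D1 = 3 × D2 (one quarter of savings in months 6-12) | 4.0 |

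The factor can lie on either side of 1, so neither size nor direction is fixed by the documents.

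**The case against.** The best defence is that Section 3.7 itself sends the reader to Table 2, and that a six-month look-back fits surveys held every six months. The Abstract describes baseline, midline and endline surveys, Section 3.6 assesses both arms at the same time points, and Section 3.13 analyses months 0, 6 and 12. The EQ-5D mismatch suggests that the two-time-point wording in Section 3.7 is loose summary. The treatment-cost rows, read with the hospital-care costs named in Section 3.7, also support some collection of hospital use at month 6. All of this stands. It makes Table 2 the likelier intent, and it means the loss of half of follow-up, which a reader might infer, is not established: it follows only if Section 3.7 is applied as written. The defence does not remove the contradiction, because Section 3.7 names its two time points explicitly and the cost rows do not name days or visit counts.

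Two other sources might fill a gap. The complications item in Section 3.7 stands outside the six-month clause and names the same conditions as the composite, but it does not record admission. Complications are also noted at counselling sessions, but only the intervention arm has those, so they would not close the gap evenly.

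On ratio (3), the six months can be read as the recall period of each survey, with cost available for each interval. That is possible, so a reader should not infer that the windows mismatch under every reading. Against it, no text adds the two windows together, and the cost-ratio rows marked at both months 6 and 12 in Table 2 cover only blood pressure and quality of life.

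A reader might also count scheduled deliveries in Table 2 and find 3 of 5 before month 6 (presentation and booklet at month 0, call at month 3), and take this as the size of the bias. It is not: deliveries are not costs, early deliveries can save days later, and of the three consultations costed in Section 3.9 only one precedes month 6.

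**Conclusion.** Wrong as written, in a limited form. The two schedules contradict each other for the hospital-use items and for EQ-5D. Applied literally, Section 3.7 leaves 6 of 12 months without questions on non-fatal admissions, hospital days and doctor visits. If Table 2 governs, the composite misses nothing, and what remains is that month-6 hospital days and visit counts are implied rather than stated.

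Ratio (3) sets a cost with no stated window against six months of hospital days. The mismatch rests on the inference that cost is the 12-month total. Given that, the error factor is 1 + D1/D2, which cannot be evaluated from the documents. It would be tempting to say that the ratio overstates the cost per day; that holds only if days are saved in both halves of the year, which the documents do not tell us. The primary blood pressure outcome is not affected.

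**What to change.** - In Section 3.7, change the collection times to months 0, 6 and 12 in both arms, with the six-month look-back each time, for hospitalisation, hospital days and doctor visits. Give EQ-5D the same three time points, as Table 2 already does.
- State that the two follow-up windows (months 0-6 and 6-12) are combined: an event in either counts for the composite, and hospital days and visits are summed.
- Restate ratio (3) in Section 3.13 as cost and hospital days over the same 12 months.
- Rows for hospital days and doctor visits in Table 2 would make the schedule visible in one place.

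The cost is a change of wording and a few extra minutes at the month-6 interview, which is already scheduled in both arms.

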### 3.8. Outcome Evaluation

The primary effectiveness of the outcome will be evaluated by changes in the SBP and DBP of the patients from baseline to final follow-up at 12 months post-intervention. The secondary outcome measures will include (1) BP controlled to target (SBP < 140 mmHg and DBP < 90 mmHg); (2) composite outcome of death (all-cause) or hospital admission due to CHD, heart failure, or stroke; (3) incremental cost per HRQoL gained from baseline to end of follow-up; (4) improvement in the knowledge of patients on healthy lifestyle; (5) change in dietary salt intake; (6) change in quality of life; (7) change in the prevalence of current smokers; and (8) the treatment adherence rate. Hypertensive patients with poor adherence to their treatment regimens experience uncontrolled blood pressure. Adherence to hypertension treatment is defined as following the treatment regimen agreed to with their physician. According to the previous literature [29,30,31], a reduction of 5 mmHg of SBP is considered clinically relevant as it has been found to be significantly associated with a risk reduction in CHD, stroke, and other serious cardiovascular events. Health service utilization parameters will include the number and reason for visits to physicians and hospital admission, and when further complicated, the death of the patient. The cost-effectiveness measures are incremental cost per mmHg BP reduction or cost per HRQoL gained from baseline to end of follow-up at 12 months. For determining dietary salt intake level, a 24 h urinary sodium measurement will be opted.

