## Abstract

The aim of this multi-country, cluster-randomized trial is to test the impact of pharmacy-based health promotion to reduce the blood pressure of individuals with hypertension over a 12-month period in Bangladesh and Pakistan. The trial will be implemented with two arms. In Bangladesh, the estimated sample size is around 3600 hypertensive patients. In Pakistan, we will select samples equivalent to 10% of the participants from Bangladesh, comprising 360 hypertensive patients from four pharmacies. Community pharmacies will be randomized into one of two parallel groups (allocation ratio 1:1). Pharmacy professionals in the treatment arm will provide their patients with educational training and counseling, as well as phone calls/mobile text messages and care coordination in the health sector, as part of the intervention. The study will be conducted in three phases: a baseline survey with intervention, a midline survey with intervention and follow-up, and an endline survey with impact evaluation. The primary outcome of the study will be BP. The secondary outcomes will be BP controlled to target, treatment adherence, quality of life, mortality or hospital admission rates resulting from hypertension and its related complications, incremental cost per health-related quality of life gained, knowledge on healthy lifestyle and dietary behavior, and change in the prevalence of current smoking status.

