### 2.1. Hypothesis

The study hypothesizes that hypertensive patients receiving the community pharmacy-based health intervention will achieve the following outcomes:Reduced systolic and/or diastolic BP;Improved treatment adherence and BP control to target levels;Reduced hospitalization and death due to cardiovascular events;Positive changes in lifestyle behaviors;Increased in HRQoL.

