## 3. Methods

### 3.1. Study Design and Settings

A two-arm parallel-group cluster-randomized controlled trial (cRCT) will be conducted among hypertensive patients in Bangladesh and Pakistan. In the first stage, two districts in Bangladesh were chosen randomly: Rangpur district and Chuadanga district. In the second stage, from each district, one subdistrict was selected randomly: Pirganj and Alamdanga. Finally, 20 pharmacies were chosen from each subdistrict to reach our target sample. The overall flow of the study is shown in Figure 1. Randomization clusters are community pharmacies. Each country will follow a two-arm cRCT design. According to a 4.65% BP reduction with a standard deviation of 49.78 [27], the estimated sample size for Bangladesh is around 3600 at 80% power and 5% significance. Approximately 10% of participants will be selected based on a Bangladesh sample from Pakistan (360 hypertensive patients from four pharmacies). The average number of hypertensive patients per pharmacy is 90. Due to financial limitations and logistical challenges, it is necessary to choose 10% of the participants from Pakistan. This decision was primarily influenced by the availability of resources and the specific focus of our research project. These limitations included budget constraints that impacted the scope of the study and logistical challenges related to the larger geographic and infrastructural differences between the two countries. Conducting a full-scale study in Pakistan similar to Bangladesh is not feasible with the available resources. However, by including participants from Pakistan, we aim to enhance the diversity within our study population, despite some similarities in sociodemographic profiles and health behaviors between the two countries.

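### The secondary death-or-admission composite does not match the hypothesis it should test, nor the questionnaire item that is to supply its admissions

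*Protocol article*

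**What the plan says.** The protocol article describes events of death and admission in several places.

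- **Section 3.8 (Outcome Evaluation)** gives the only full definition, as the second of eight secondary outcomes: "composite outcome of death (all-cause) or hospital admission due to CHD, heart failure, or stroke". The same section lists, among health service utilization parameters, "the number and reason for visits to physicians and hospital admission".
- **Section 2.1 (Hypothesis)** expects "Reduced hospitalization and death due to cardiovascular events".
- **The abstract** lists "mortality or hospital admission rates resulting from hypertension and its related complications" among the secondary outcomes.
- **Section 3.7 (Data Collection)** asks, with a six-month look-back, about "occurrence of any adverse health condition related to hypertension requiring hospitalization". It also asks for days in hospital and visits to doctors.
- **Table 2** labels the row "Composite outcome of death or hospital admission".
- **Section 3.13**, in the cost-effectiveness part, uses the unit "one hospital admission reduced".

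No sentence says which wording takes precedence.

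**The concern.** Two links in the chain from hypothesis to data look broken.

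The first runs from hypothesis to outcome. The hypothesis claims an effect on events with a cardiovascular cause, while the outcome counts deaths whatever their cause. A difference in the composite could come from deaths that the hypothesis says nothing about. A real effect on cardiovascular death could also be diluted by deaths that the intervention does not touch.

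The second runs from outcome to data. The outcome needs admissions for three named diagnoses. The questionnaire asks for admissions related to hypertension, so someone has to decide at interview whether an admission qualifies.

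The introduction names the impact on mortality and hospital admission rates, together with cost-effectiveness, as what has not been studied in these two countries. This composite is the listed effectiveness outcome that addresses deaths and admissions, so its meaning should be settled before results are seen.

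**Working it through.** **1. The plan's own figure.** Section 3.1 bases the Bangladesh sample on blood pressure: "According to a 4.65% BP reduction with a standard deviation of 49.78", with 80% power and 5% significance. Tests are two-sided (Section 3.13) and allocation is 1:1. Per arm, n = 2 × (1.960 + 0.842)² × 49.78² / 4.65² = 2 × 7.849 × 2478.05 / 21.62 ≈ 1799.04, rounded up to 1800. The total is 2 × 1800 = 3600, which is the stated size. The composite does not enter this calculation. The article gives no event rate, event count or power for it.

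**2. Deaths side by side.**

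| Place | Deaths that count |
|---|---|
| Section 3.8 | any cause |
| Section 2.1 | due to cardiovascular events |
| Abstract | resulting from hypertension and its complications |

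These are three different sets. The first contains the other two, so every death outside the cardiovascular set counts in the outcome but not in the hypothesis.

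**3. Admissions side by side.**

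| Place | Admissions that count |
|---|---|
| Section 3.8 | CHD, heart failure or stroke |
| Section 2.1 | due to cardiovascular events |
| Abstract | resulting from hypertension and its complications |
| Section 3.7 item | any condition related to hypertension |

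Section 3.7 names CHD, heart failure and stroke in its preceding item on complications, but only as examples, so the category stays open. The admission item is therefore wider than Section 3.8 for other hypertension-related conditions. It can also be narrower: a CHD admission that patient and interviewer do not attribute to hypertension fails the item's filter although Section 3.8 counts it.

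**4. Reason for admission.** Section 3.8 says that the reason will be among the parameters. The admission details listed in Section 3.7 are occurrence, days in hospital and doctor visits, without the reason. If only the Section 3.7 items were collected, the three-cause subset could not be picked out.

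**5. Who applies the filter.** Section 3.4 says that research assistants collect the data and are not blinded. Blinding is reserved for outcome evaluators. Table 1 shows that intervention patients are taught the complications of hypertension (item 2). Whether an admission is called hypertension-related could therefore differ by arm for reasons unrelated to true event rates. The documents do not show in which direction, or that it would happen.

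**6. Can this be sized?** If cardiovascular deaths are a share s of control-arm deaths, the intervention has risk ratio r on them and no effect on the rest, the all-cause risk ratio is 1 − s × (1 − r). This lies nearer to 1 than r whenever s is below 1. Neither s nor r is in the article. The composite also depends on the rate of three-cause admissions and their overlap with deaths, which are not given either. The direction is clear; a number is not available.

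**The case against.** The strongest reply is that Section 3.8 is the outcome section and its definition is complete. An abstract, a one-line hypothesis and a table label are summaries and need not repeat it. Pairing all-cause death with cause-specific admission is a defensible choice, because it avoids attributing causes of death. Since Section 3.8 records reasons for admission, and Section 3.7 treats the three diagnoses as complications of hypertension, the wider item should contain the three-cause subset.

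Much of this stands. The composite is defined, and a reader who inferred that it is undefined would go too far. The choice of all-cause death needs no defence. The hypothesis, however, is not merely a shorter form of the definition: it names a different set of deaths. The item in Section 3.7 contains the three-cause subset only if every such admission is judged hypertension-related at interview, and the reason appears in one section but not in the other.

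A reader might also infer from the Table 2 label and the cost-effectiveness unit that a further definition, admission for any cause, is in play. The documents do not support that. Neither place says so outright, and both are probably shorthand.

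**Conclusion.** The point holds as a mismatch between hypothesis, outcome and data item. The composite in Section 3.8 does not test the hypothesis in Section 2.1 as worded. The admission item in Section 3.7 does not correspond to the three causes and relies on attribution at an unblinded interview.

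Its weight is moderate. The outcome is secondary, and neither the sample size nor the primary blood pressure analysis depends on it. No size can be given without outside assumptions on mortality, the cardiovascular share of deaths and admission rates. A contrast of risk ratios for death alone would not describe the composite in any case. It would also be tempting to call this the trial's safety endpoint, but the article never does so, and Section 3.11 deals with adverse events separately.

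The conclusion assumes that the item in Section 3.7 is close to what will be asked in the field. If the full questionnaire already records every admission with its reason, the data-capture part falls away and the mismatch between hypothesis and outcome remains.

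**What to change.** 1. State that the composite in Section 3.8 governs.
2. Reword the hypothesis in Section 2.1 and the outcome in the abstract to match it, and complete the Table 2 label with the causes.
3. Change the admission item in Section 3.7 to record every admission with its date and stated reason, without asking first whether it was related to hypertension. This also brings it into line with the parameters in Section 3.8.
4. Derive the CHD, heart failure or stroke subset afterwards by one written rule applied in both arms. The blinded outcome evaluators of Section 3.4 could apply it.

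This takes wording changes and one broader questionnaire item, with no extra visit or staff. The only downside is that the item becomes slightly longer.
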